### Diagnostic accuracy

3.3

The second step of the analytic approach will be to update the score thresholds for determining risk. Receiver Operating Characteristics (ROC) curve analysis will be used to define the most appropriate cut-off scores for stratifying low, moderate, and high-risk use. Based on the new thresholds, outcomes from the diagnostic interview outcomes will be used to determine the number of true positive (TP), true negative (TN), false positive (FP), false negative (FN) cases for each diagnosis within the sample. Where trueness or falseness is determined by the interview, and positivity or negativity is determined by the ASSIST risk category, based on the theoretical alignment between low-risk ASSIST and mild SUD/hazardous use; moderate-risk ASSIST and moderate SUD/harmful use; and high-risk ASSIST and severe SUD/dependence. For example, TP in the context of ICD-11 dependence would represent the number of high-risk ASSIST cases (i.e., positivity) who were diagnosed with dependence (i.e., trueness) on the interview. Similarly, TN would represent the number of low and moderate risk ASSIST cases who were not diagnosed with dependence. TP, TN, FP and FN parameters will then be used to calculate sensitivity, specificity, positive predictive value (PPV) and negative predictive value (NPV) for each substance, at each risk threshold, i.e., for DSM-5-TR between no disorder vs. any disorder (low risk threshold); between no disorder/mild SUD vs. moderate/severe SUD (moderate risk threshold); and between non-severe vs. severe SUD (high risk threshold). Parallel analysis will occur based on ICD-11 classifications.

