#### Recruitment

2.2.2

A stratified sampling strategy will be employed to target individuals across the spectrum of risk for each of the five substances included in the Pitjantjatjara ASSIST (“*the app*”, i.e., alcohol, tobacco, cannabis, methamphetamine and inhalants). Since *the app* focuses on these five substances only, and uses existing WHO-ASSIST 3.1 cut-off scores to determine three corresponding levels of risk for each (i.e., low, moderate or high), there are a total of 15 (5x3) possible substance/risk combinations. We will aim to recruit a minimum of 40 individuals to satisfy each of those outcomes (e.g., 40 participants each for low, moderate and high-risk, for each of the substances This could require up to 600 participants, though the total will likely be lower since many use multiple substances. Recruitment will occur until we meet the minimum number for each group, or until the investigators deem it unnecessary to continue. Further details related to the power calculations is found in section 3.5. *Sample Size and Power Calculations* below.

To capture a broad range of participants, we will recruit from a variety of health and welfare settings. The goal is to recruit individuals who are likely to be engaged in low and/or moderate risk alcohol, tobacco or other drug use (e.g., from general health and welfare settings), and those who are more likely to be engaged in use which places them at higher-risk of dependence (e.g., from withdrawal services or other inpatient/outpatient treatment settings). Recruitment will occur at seven different sites across South Australia, by word-of-mouth at each service or setting, where Aboriginal health workers will approach potential participants directly.

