#### Sensitivity and specificity

3.3.1

Sensitivity describes the proportion of correctly identified true cases, and thus can be calculated by dividing the number of true positive cases by the total number of positive cases in the sample (TP/TP + FN). On the other hand, Specificity describes the proportion of correctly identified negative cases, and thus can be calculated by dividing the number of true negative cases by the total number of negative cases in the sample (TN/TN + FP). ROC curves can be calculated for each substance and level of risk by plotting sensitivity on the x-axis, and (1-specificity) on the y-axis. The point at which the distance from the ROC curve (AUC) to the diagonal is maximised (Youden's *J*) can then be used to identify the most appropriate cut-off scores for each substance, at each level of risk. In effect, AUC describes the probability, if given one TP, that that TP will score higher than one TN on the test. The criterion for AUC will be set at ≥ 0.71, to indicate at least better than acceptable accuracy [42].

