### Sample Size and Power Calculations

**3.5**

For the validity assessments, a series of power calculations were conducted to determine the minimum sample size needed to detect a large between-groups effect, with type-I, and type-II error rates of 5 % (corresponding to α = 0.05), and 10 % (corresponding to an *a priori* power of 90 %) respectively. Where possible, we will also aim to recruit a 1:1 ratio of participants for each group (i.e., positive/negative cases), and so a 1:1 ratio of participants was used here. Using these parameters as default, we conducted the following power calculations in G-power [43].

For each regression model assessing concurrent validity, it was determined that a minimum of 111 participants are needed for each model (corresponding to line-of-best-fit slope of 0.3). For each logistic regression model assessing concurrent validity with the independent assessment, a total sample size of 62 using each substance was determined. The additional parameters used in this analysis included a probability of reaching diagnosis in the diagnosis present group of 0.70 (corresponding to a sensitivity of 70 % and an Odds Ratio of 2.33 [0.70/0.30]), versus a chance probability (i.e., 50%) in the diagnosis absent group. These parameters yielded a total sample size of 62 individuals (approximately 31 in each group diagnosis present/absent assuming 1:1 sampling). For each ANOVA model assessing discriminant validity, a minimum of 96 participants using each substance are required to power the analysis (corresponding to *η*^2^ = 0.14 [44]). Based on this, the minimum number of participants to detect a large effect (Cohens’ *d* > 0.80 [45]) was 38 participants for each group. This corresponds to thirty-eight low risk, thirty-eight moderate risk, and thirty-eight high-risk individuals for each substance (which equals approximately 114 participants for each given substance). For the reliability assessment, we also calculated the minimum sample size required to detect reliability coefficients >0.70, setting the type-I error rate to 0.05, with a minimum power of 0.90, with the number of scale items equal to 4 (tobacco) or 5 (all other substances). This method has been suggested previously [46] and has been used widely in health and medical research settings [47]. The result was a minimum sample size of 38 for a 5-item scale, and 40 for the 4-item scale. We elected to use 40 as the minimum sample size required for consistency.

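### New cut-offs and their accuracy come from the same participants, so the accuracy indices reported at those cut-offs are biased upward by a moderate amount

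*Protocol article*

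**What the plan says.** Section 3.3 (Diagnostic accuracy) sets an order of steps. First, "Receiver Operating Characteristics (ROC) curve analysis will be used to define the most appropriate cut-off scores for stratifying low, moderate, and high-risk use". Section 3.3.1 gives the rule: the point of maximum Youden's J "can then be used to identify the most appropriate cut-off scores for each substance, at each level of risk".

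Next come the counts: "Based on the new thresholds, outcomes from the diagnostic interview outcomes will be used to determine the number of true positive (TP", with true negatives and false positives, through to "false negative (FN) cases for each diagnosis within the sample". Sensitivity, specificity, PPV and NPV are calculated from these counts "for each substance, at each risk threshold", for DSM-5-TR and in parallel for ICD-11. Section 3.3.3 adds likelihood ratios, clinical utility indices and weighted kappa.

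Section 2.2.2 (Recruitment) says that the app already "uses existing WHO-ASSIST 3.1 cut-off scores to determine three corresponding levels of risk for each". The recruitment minimum there is "40 participants each for low, moderate and high-risk, for each of the substances". Section 3.5 arrives at a similar size, 38 per risk group, "which equals approximately 114 participants for each given substance".

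The only resampling the article describes is the bootstrap for the reliability coefficients in section 3.1.1.

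**The concern.** Youden's J is sensitivity + specificity - 1. The cut-off that maximises it is the one at which chance variation in this sample happens to favour that sum. Reporting sensitivity and specificity at that cut-off, in the same people, reports the favourable chance variation as accuracy. The same counts feed PPV, NPV, the likelihood ratios and the clinical utility indices. Weighted kappa is affected too if it uses the new risk categories; section 3.3.3 does not say which categories it uses.

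Section 3 lists diagnostic accuracy among the primary outcomes. The Discussion expects an accurate instrument to inform estimates of how common substance use disorders are, so overstated sensitivity and specificity could carry into later work.

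The number of data-driven 2x2 tables is at most 5 substances x 3 thresholds x 2 classification systems = 30. Table 3 labels its screen-negative row as no use. If that boundary is fixed in advance, 5 x 2 x 2 = 20 remain.

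**Working it through.** **Plan's own figure.** The article gives no expected value, precision or sample size for sensitivity, specificity, PPV or NPV, so there is nothing to reproduce. The question is how large the bias is at the planned size.

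**Inputs from the article.** 3 x 40 = 120 participants per substance (section 2.2.2) or 3 x 38 = 114 (section 3.5); cut-off at maximum J (section 3.3.1); AUC criterion 0.71 (section 3.3.1).

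**Assumptions not in the article.** Scores normal in cases and non-cases with equal SD of 8, rounded to integers from 0 to 39; true AUC of 0.71, 0.80 or 0.90. The distance between group means is √2 x Φ⁻¹(AUC) standard deviations. The number of cases is varied because the minimum of 40 is set by ASSIST risk level, not by interview diagnosis.

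**Method.** In each of 4,000 simulated samples per setting, the cut-off maximising J was found. Apparent accuracy in that sample was compared with the true accuracy of the same cut-off under the model.

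| Cases / non-cases | AUC | Sensitivity, apparent vs true | Specificity | PPV | NPV | J |
|---|---|---|---|---|---|---|
| 40 / 80 | 0.71 | 0.699 vs 0.649 | 0.661 vs 0.635 | 0.526 vs 0.485 | 0.824 vs 0.791 | 0.360 vs 0.284 |
| 40 / 80 | 0.80 | 0.765 vs 0.721 | 0.729 vs 0.708 | 0.601 vs 0.566 | 0.867 vs 0.841 | 0.495 vs 0.429 |
| 40 / 80 | 0.90 | 0.848 vs 0.813 | 0.822 vs 0.806 | 0.716 vs 0.688 | 0.918 vs 0.899 | 0.670 vs 0.618 |
| 60 / 60 | 0.71 | 0.692 vs 0.658 | 0.663 vs 0.627 | 0.685 vs 0.649 | 0.697 vs 0.659 | 0.355 vs 0.285 |
| 60 / 60 | 0.80 | 0.761 vs 0.732 | 0.728 vs 0.698 | 0.746 vs 0.717 | 0.763 vs 0.732 | 0.489 vs 0.430 |
| 60 / 60 | 0.90 | 0.844 vs 0.820 | 0.825 vs 0.799 | 0.833 vs 0.809 | 0.846 vs 0.822 | 0.668 vs 0.619 |
| 20 / 100 | 0.71 | 0.721 vs 0.634 | 0.659 vs 0.644 | 0.324 vs 0.280 | 0.927 vs 0.903 | 0.380 vs 0.278 |
| 20 / 100 | 0.80 | 0.779 vs 0.707 | 0.728 vs 0.716 | 0.392 vs 0.353 | 0.946 vs 0.928 | 0.507 vs 0.423 |
| 20 / 100 | 0.90 | 0.863 vs 0.799 | 0.824 vs 0.813 | 0.523 vs 0.485 | 0.969 vs 0.955 | 0.687 vs 0.613 |

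**Reading the table.** With 40 or 60 cases, the difference per index runs from 0.016 (specificity, 40/80, AUC 0.90: 0.822 - 0.806) to 0.050 (sensitivity, 40/80, AUC 0.71: 0.699 - 0.649). On J it runs from 0.668 - 0.619 = 0.049 to 0.360 - 0.284 = 0.076. With 20 cases, sensitivity is overstated by 0.863 - 0.799 = 0.064 to 0.721 - 0.634 = 0.087. A repeat with 20,000 samples per setting gave 0.062 to 0.085 for that last range and similar values for sensitivity, specificity and J elsewhere.

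**Does the remedy work?** A bootstrap optimism correction, with the cut-off search repeated in every resample (1,000 samples, 100 resamples each), was tried with 38 cases and 76 non-cases:

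| AUC | Sensitivity: apparent, corrected, true | Specificity: apparent, corrected, true |
|---|---|---|
| 0.71 | 0.699, 0.662, 0.651 | 0.656, 0.636, 0.631 |
| 0.80 | 0.767, 0.735, 0.725 | 0.723, 0.706, 0.702 |
| 0.90 | 0.849, 0.823, 0.815 | 0.820, 0.806, 0.802 |

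At AUC 0.80 the error in sensitivity falls from 0.767 - 0.725 = 0.042 to 0.735 - 0.725 = 0.010, so most of the bias is removed, though not all. A cut-off fixed in advance was essentially unbiased: estimated 0.731 and 0.711 for sensitivity and specificity, against true values of 0.735 and 0.713.

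**The case against.** **The analysis plan is not shown.** It is said to be an appendix and could contain an internal validation step or a table at the existing cut-offs. This stands in part. A reader might infer that the study will never report accuracy at the cut-offs the app now uses; the article alone cannot support that. But the order of steps in section 3.3 is stated, not left open, and as stated it gives biased figures.

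**No success criterion changes.** This stands. The only accuracy criterion in section 3.3 is AUC of at least 0.71, and AUC does not depend on the chosen cut-off. Sensitivity, specificity, PPV and NPV have no pass mark. A reader might infer that the study could wrongly declare the app accurate under its own rule; the article does not support that.

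**The bias is smaller than sampling error.** With 40 cases and sensitivity near 0.72 the standard error is √(0.72 x 0.28 / 40) = 0.071. With 80 non-cases and specificity near 0.71 it is √(0.71 x 0.29 / 80) = 0.051. The bias is indeed below these. Unlike sampling error, though, it always favours the app: all four indices were inflated in every setting tried.

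**Small cells are not planned.** The article aims for 40 per risk group and, where possible, equal numbers of positive and negative cases. The 20-case figures are therefore a contingency. They remain possible, because the 40 refers to risk level rather than diagnosis and section 2.2.2 lets the investigators stop recruitment before the minimums are met.

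**The WHO cut-offs cannot take over as the main analysis.** This stands. Three risk levels give two boundaries, whereas section 3.3 evaluates three thresholds. Updating the thresholds is a stated aim for an instrument whose items were modified. Accuracy at the existing cut-offs can only sit alongside.

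**Youden's J is worded as something that can be used.** It is the only rule named, and any rule that optimises the cut-off in the same sample shares the problem.

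**Conclusion.** The point holds as a moderate defect that should be fixed. As written, section 3.3 selects cut-offs and measures their accuracy in the same participants, which biases a primary outcome upward. At the planned size (40 to 60 cases among 120, true AUC 0.71 to 0.90) the bias is about 2 to 5 percentage points per index and about 0.05 to 0.08 on J. If only 20 participants have the diagnosis, sensitivity is overstated by about 6 to 9 points.

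These sizes rest on an assumed equal-variance binormal score, and the article itself anticipates possible excess zeros. The upward direction follows from the procedure; the exact size does not. The reliability and validity criteria in sections 3.1 and 3.2 do not use the new cut-offs and are untouched.

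**What to change.** Amend section 3.3, and the analysis plan if it does not already do this, before the data are analysed:

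1. For each new cut-off, report bootstrap optimism-corrected or cross-validated sensitivity, specificity, PPV and NPV, repeating the whole cut-off search in every resample. Treat the likelihood ratios and clinical utility indices the same way, and weighted kappa if it uses the new categories.
2. Give a bootstrap interval for each cut-off.
3. Label any uncorrected value as apparent accuracy.
4. Alongside this, not in its place, report accuracy at the existing WHO-ASSIST 3.1 cut-offs for the two boundaries they define (low/moderate and moderate/high), as a comparator free of selection bias in this sample.

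The cost is some analysis code, a few sentences of text and slightly less favourable figures. No extra participants, visits or data are needed.

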#### Likelihood ratios and clinical utility indices

3.3.3

Finally, we will also compute a range of additional metrics, including likelihood Ratios for positive (LR+) and negative (LR-) tests; Clinical Utility Index for positive (CUI+) and negative (CUI-) tests; and Cohen's weighted Kappa (interrater agreement). LR + describes the ratio of true cases to false cases, while LR-describes the likelihood of true non-cases to false non-cases. Higher ratios indicate better accuracy. CUI+ is the product of sensitivity and positive predictive value, while CUI- is the product of specificity and the negative predictive value. Finally, weighted-kappa will be used to indicate the level of agreement between risk outcomes from the ASSIST and diagnostic classifications from the clinical interview.

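### Cut-off-based accuracy indices are to be computed at cut-offs chosen by maximum Youden's J in the same participants, so they will be optimistic on average; AUC is not affected

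*Protocol article*

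**What the plan says.** The app currently "uses existing WHO-ASSIST 3.1 cut-off scores to determine three corresponding levels of risk" (section 2.2.2). Section 3.3 plans to replace those thresholds: "Receiver Operating Characteristics (ROC) curve analysis will be used to define the most appropriate cut-off scores for stratifying low, moderate, and high-risk use". Section 3.3.1 gives the selection rule. The point where the ROC curve lies furthest from the diagonal (Youden's J) "can then be used to identify the most appropriate cut-off scores for each substance, at each level of risk".

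Evaluation follows directly in section 3.3: "Based on the new thresholds, outcomes from the diagnostic interview outcomes will be used to determine the number of true positive (TP", along with the other three cells, ending with "false negative (FN) cases for each diagnosis within the sample". The resulting "parameters will then be used to calculate sensitivity, specificity, positive predictive value (PPV) and negative predictive value (NPV) for each substance", at each risk threshold and under both classification systems. Section 3.3.3 adds likelihood ratios and clinical utility indices, which are functions of the same counts, and says "weighted-kappa will be used to indicate the level of agreement between risk outcomes from the ASSIST and diagnostic classifications". It does not restate which cut-offs define those risk outcomes.

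The only accuracy measure with a pass mark is AUC, at 0.71 or more (section 3.3.1). On numbers, section 2.2.2 says "We will aim to recruit a minimum of 40 individuals to satisfy each of those outcomes", meaning each substance and risk-level combination. Section 3.5 gives no sample size or precision for the accuracy indices.

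**The concern.** The same participants choose each cut-off and then grade it. The maximum of an estimated curve tends to fall where chance has pushed the curve up, so its height overstates what that cut-off will do in new people. Every index built on the resulting two-by-two counts inherits this.

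Section 3 names diagnostic accuracy as a primary outcome, and section 3.3 means the new cut-offs to replace the existing ones. Services adopting the app would then read sensitivities and specificities somewhat better than they should expect. The article guards against comparable problems elsewhere: a 10,000-sample bootstrap for internal consistency (section 3.1.1) and AIC/BIC comparison for the exploratory regressions (section 3.2.1). It states no such guard here.

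**Working it through.** **No plan figure to reproduce.** The article gives no expected value, precision or sample size for sensitivity, specificity or J. The direction of the bias can be shown by argument; its size needs simulation under stated assumptions.

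**Direction.** Let J(c) = sensitivity(c) + specificity(c) − 1. Let Ĵ(c) be its sample estimate, c* the cut-off that maximises Ĵ, and c₀ the cut-off that maximises the true J. By construction Ĵ(c*) ≥ Ĵ(c₀), so the mean of Ĵ(c*) is at least J(c₀), and J(c₀) ≥ J(c*). The optimism, mean Ĵ(c*) − mean J(c*), therefore has two non-negative parts: the apparent J exceeds the best attainable J, and the chosen cut-off falls short of the best.

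**Inputs.**
- From the article: selection by maximum J, evaluation in the same sample, and a minimum of 40 per risk level, so about 3 × 40 = 120 per substance.
- Assumed: integer scores 0 to 39; normal scores with SD 8 in both groups; non-case mean 10; case mean 10 + 8 × √2 × z(AUC). For example, AUC 0.71 gives z = 0.553 and a case mean of about 16.3.
- Assumed splits: 40 cases and 80 non-cases as the central case, with others for range. The quotas are by ASSIST category, not by interview diagnosis, so the true split is unknown.
- 20,000 simulated studies per scenario.

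**Result at 40 cases and 80 non-cases.**

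| True AUC | Apparent J | Best attainable J | True J at chosen cut-off | Optimism | Sensitivity | Specificity | Studies overstated |
|---|---|---|---|---|---|---|---|
| 0.71 | 0.358 | 0.304 | 0.284 | 0.074 | +4.9 points | +2.5 points | 83% |
| 0.80 | 0.493 | 0.448 | 0.429 | 0.064 | +4.2 points | +2.2 points | 81% |
| 0.90 | 0.670 | 0.635 | 0.618 | 0.052 | +3.5 points | +1.8 points | 79% |

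At AUC 0.71 the two parts are 0.358 − 0.304 = 0.054 and 0.304 − 0.284 = 0.020, which sum to 0.074. A two-by-two kappa is overstated by a similar amount: 0.331 against 0.262, 0.462 against 0.401, and 0.641 against 0.591. The plan's weighted kappa was not simulated, so these values are only a guide. The mean error of the empirical AUC was 0.000 in every scenario.

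**Optimism in J for other splits (AUC 0.71, 0.80, 0.90).**
- 80 cases, 40 non-cases: 0.073, 0.064, 0.052
- 60 and 60: 0.068, 0.058, 0.047
- 20 and 100: 0.100, 0.088, 0.074
- 200 and 400: 0.025, 0.021, 0.016
- 40 and 560 (6,000 studies each): 0.060, 0.052, 0.042

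Adding non-cases alone barely helps, because the number of cases drives the bias.

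**Variation of the chosen cut-off at 40 and 80.** The central 95% of selected values runs from 7 to 20 around an optimum of 14 (AUC 0.71), 10 to 20 around 15 (0.80), and 14 to 22 around 18 (0.90). The average cost in true J is small: 0.304 − 0.284 = 0.020, 0.448 − 0.429 = 0.019, and 0.635 − 0.618 = 0.017. The curve is flat near its top. Five substances, three thresholds and two classification systems give up to 5 × 3 × 2 = 30 such selections.

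**Does correction work?** In a separate run (AUC 0.75, SD 7, 40 and 80, 400 studies with 200 bootstrap resamples each), apparent J was 0.418, true J 0.348 and corrected J 0.367. The bias falls from 0.070 to 0.019.

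**The case against.** The strongest reply is that this is a condensed article. Section 3 refers to a detailed SAP appendix, and internal validation is often specified there. Section 3.3.1 is also worded permissively about using Youden's J. This stands as a limit: the SAP may contain a correction. It does not remove the point, because the article itself states the selection rule, the order of steps and the sample in which the counts are made. Followed as written, that procedure gives optimistic figures.

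The second reply concerns size. The bias is an average, and about 20% of simulated studies at 40 and 80 show no overstatement. It is of the same order as, and a little below, the sampling SD of apparent J (about 0.065 against 0.078 at AUC 0.75). The quotas are minimums within a total of up to 600, so case numbers could be larger and the bias smaller. All of this stands and is why a range is given.

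Three stronger readings are tempting, and the documents do not support them.
- A reader might infer that every accuracy result is inflated. AUC needs no cut-off, so the article's only accuracy pass mark is untouched.
- A reader might infer from the wide spread of selected cut-offs that the new thresholds will perform poorly. The average loss is only about 0.02 in true J.
- A reader might conclude that an existing cut-off should be replaced only when the new interval excludes it. That is a separate decision rule. It does not follow from the bias, and with intervals this wide it could often block the updating that section 3.3 sets out to do.

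**Conclusion.** The point holds for the cut-off-based indices: sensitivity, specificity, PPV, NPV, likelihood ratios and clinical utility indices. It holds for kappa if, as the order of sections 3.3 to 3.3.3 suggests, kappa uses the new thresholds. At 40 cases and 80 non-cases the overstatement is moderate, about 0.05 to 0.07 in J. It is larger with fewer cases and small with several hundred participants in both groups. The direction follows from the stated procedure. The size rests on assumed equal-variance binormal scores and assumed case numbers, and the conclusion is subject to what the unseen SAP appendix says. It should be put right before analysis, but it does not undermine the design or the AUC criterion.

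**What to change.** In sections 3.3 and 3.3.1, and in the SAP if it does not already do so:
- Report the cut-off-based indices after bootstrap optimism correction, repeating the cut-off search inside each resample; cross-validation that repeats the search is an alternative. Show the uncorrected values alongside.
- Give a bootstrap 95% interval for each new cut-off.
- State in section 3.3.3 which cut-offs the weighted kappa uses.

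This takes some wording and a little code, with no new data. The price is that reported sensitivity and specificity fall by a few points. The correction removes most but not all of the bias: in the run above, 0.019 of 0.070 remained.

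### Sensitivity, specificity, PPV, NPV and clinical utility indices are taken from raw counts in a sample whose mix is driven by tier minimums and treatment-service recruitment, so they describe no identifiable screening setting

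*Protocol article*

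**What the plan says.** On recruitment, section 2.2.2 of the protocol article states: "A stratified sampling strategy will be employed to target individuals across the spectrum of risk for each of the five substances". The strata are levels of the index test itself, since the app "uses existing WHO-ASSIST 3.1 cut-off scores to determine three corresponding levels of risk for each". The target is a minimum: "We will aim to recruit a minimum of 40 individuals to satisfy each of those outcomes". Stopping is partly discretionary: "Recruitment will occur until we meet the minimum number for each group, or until the investigators deem it unnecessary to continue". The same section looks for lower-risk people in general health and welfare settings and for higher-risk people in withdrawal and other treatment services. Section 3.5 adds, for positive and negative cases: "Where possible, we will also aim to recruit a 1:1 ratio of participants for each group".

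On analysis, section 3.3 counts true and false positives and negatives in the study sample, at cut-offs re-derived from the same data, and continues: "TP, TN, FP and FN parameters will then be used to calculate sensitivity, specificity, positive predictive value (PPV) and negative predictive value (NPV". Sections 3.3.1 and 3.3.2 give these as plain ratios of counts. Section 3.3.2 explains PPV and NPV as the probability that a person with a given screen result is truly a case or a non-case, without limiting this to the mix recruited. Section 3.3.3 multiplies sensitivity by PPV for CUI+ and specificity by NPV for CUI-. The limitations in section 4 cover self-report and language, not the recruitment mix.

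**The concern.** Recruitment acts on the accuracy table in two ways.

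- **Sampling on the ASSIST tier.** If moderate and high tiers are over-represented relative to the people the app would screen, test-positives are over-represented. That raises apparent sensitivity and lowers apparent specificity, and CUI moves with them. The Youden cut-offs in section 3.3.1 use the same two quantities.
- **Enrichment with cases.** Treatment-service recruitment, and any move towards a 1:1 case ratio, raises the share of people with a diagnosis. PPV then rises and NPV falls even if the test is unchanged.

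The app is meant for screening linked to brief intervention (section 1). A service that reads the published PPV as section 3.3.2 explains it would take it as the chance that its own positive screens are true cases. The raw figure would not support that reading.

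**Working it through.** **The plan's own figures.** Section 2.2.2: 5 substances x 3 tiers = 15 cells, and 15 x 40 = 600, as stated. Section 3.5: 3 x 38 = 114 per substance, as stated. Both reproduce.

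**How far the mix can move.** Forty high-risk people for a substance are 40/120 = 33% if the three cells are filled exactly, and 40/600 = 6.7% if the total reaches 600 and nobody else is high-risk for that substance. The mix is driven by the design but not set at one value.

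**Mechanism 1: sampling on the tier (high-risk threshold, dependence).** Assumed, because the article gives neither: screening tier mix 70/22/8% (low/moderate/high) and dependence in 2/15/60% of those tiers.

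- Cases in the screening mix: 0.70 x 0.02 = 0.014; 0.22 x 0.15 = 0.033; 0.08 x 0.60 = 0.048; total 0.095.
- Non-cases: 0.686, 0.187 and 0.032; total 0.905.

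| | Screening mix | Equal tiers |
|---|---|---|
| Case share | 0.095 | 0.77/3 = 0.257 |
| Sensitivity | 0.048/0.095 = 0.51 | 0.60/0.77 = 0.78 |
| Specificity | 0.873/0.905 = 0.96 | 1.83/2.23 = 0.82 |
| PPV | 0.048/0.08 = 0.60 | 0.20/0.333 = 0.60 |
| NPV | 0.873/0.92 = 0.95 | 1.83/2.00 = 0.92 |
| CUI+ | 0.505 x 0.60 = 0.30 | 0.779 x 0.60 = 0.47 |

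High-tier PPV does not move, because sampling by tier leaves the diagnosis rate within a tier as it was. That protection needs the tiers to stay as sampled, and it does not extend to a threshold that pools two tiers. With assumed disorder rates of 5/30/75%, PPV for moderate-or-high is (0.30 + 0.75)/2 = 0.525 at equal tiers. At an 85/10/5% mix it is (0.030 + 0.0375)/0.15 = 0.45.

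**Mechanism 2: case enrichment, test properties held fixed.** Assumed sensitivity = specificity = 0.80; p is the case share.

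- PPV = 0.8p / (0.8p + 0.2(1 - p))
- NPV = 0.8(1 - p) / (0.8(1 - p) + 0.2p)
- CUI+ = 0.8 x PPV

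| p | PPV | NPV | CUI+ |
|---|---|---|---|
| 0.50 (1:1) | 0.80 | 0.80 | 0.64 |
| 0.20 | 0.50 | 0.94 | 0.40 |
| 0.10 | 0.31 | 0.97 | 0.25 |
| 0.05 | 0.17 | 0.99 | 0.14 |

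At 0.70/0.70, PPV is 0.70 at 1:1, 0.21 at 10% and 0.11 at 5%. At 0.90/0.90 it is 0.90, 0.50 and 0.32. The direction does not depend on the assumed accuracy.

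The two mechanisms are separate models. The second holds sensitivity and specificity constant, whereas the first shows them changing, so their figures must not be combined.

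**Does re-weighting repair mechanism 1?** Weights from equal tiers to 70/22/8% are 0.70 x 3 = 2.10, 0.22 x 3 = 0.66 and 0.08 x 3 = 0.24. Weighted cases are 2.10 x 0.02 + 0.66 x 0.15 + 0.24 x 0.60 = 0.042 + 0.099 + 0.144 = 0.285. Sensitivity is 0.144/0.285 = 0.51, the screening value.

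**The case against.** The strongest reply is that tier sampling preserves PPV. In the example above it is 0.60 in both columns, at a screening case share of 9.5%. A reader might infer that the tier minimums alone would make PPV fall from 0.67 (one-third cases, 0.80/0.80) to 0.31 at 10% prevalence. The documents do not support that: one-third is the share of test-positives at equal tiers, not of cases (25.7% in the example), and the 0.31 belongs to case enrichment only. This part of the reply stands.

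It does not rescue the plan. Sensitivity, specificity and CUI still shift; the moderate threshold pools two tiers; section 3.3 re-derives the cut-offs, so the final positives are not the sampled tiers; and treatment-service recruitment can change the diagnosis rate within a tier. The size of that last effect cannot be derived from the article.

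Other stronger readings also fail:

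- *The mix is fixed at 40/40/40.* Forty is a minimum, stopping is discretionary, and abstainers are recruited (section 2.2), so non-users can fill low-risk cells.
- *The 1:1 ratio contradicts the tier minimums.* The ratio concerns diagnosed cases, where possible; the minimums concern ASSIST tiers.
- *The study will infer prevalence from these figures.* Section 4 leaves disorder rates to future research, conditional on the app proving valid and reliable.

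It is also fair that the only accuracy criterion stated in section 3.3 is an AUC of at least 0.71, so no success rule rests on PPV, NPV or CUI. The detailed analysis plan is not shown and may add an adjustment. Neither point alters the formulas or the unqualified explanation of PPV that the article itself states.

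**Conclusion.** The point holds in this form: the planned sensitivity, specificity, PPV, NPV and CUI are raw ratios from a recruitment-driven mix, and they transfer to no identifiable screening setting. To say that they could describe no screening setting at all would go too far. The realised mix is unknown, and some setting might happen to resemble it; for instance, section 1 reports daily smoking in 29% of Indigenous Australians, so a high case share for tobacco is not plainly artificial.

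Under the assumed tier mix and dependence rates, tier sampling moves sensitivity by +0.27, specificity by -0.14 and CUI+ by +0.17, and leaves high-tier PPV alone. Under assumed 0.80/0.80 accuracy, enrichment to 1:1 gives a PPV of 0.80 where 5% to 20% prevalence would give 0.17 to 0.50. Every prevalence, tier mix, diagnosis rate by tier and accuracy value here is an assumption. The directions are firm; the sizes are illustrative. This should be corrected, but it does not undermine the study.

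**What to change.** In section 3.3:

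1. Report the diagnosis rate within each ASSIST tier, separately for general-health and treatment-service recruits. Recruitment setting must be kept in the analysis dataset.
2. Present sensitivity, specificity, PPV, NPV and CUI re-weighted over a stated range of tier mixes or prevalences, each labelled as assumed unless a source is given.
3. Label the raw pooled values as specific to the quota sample, and draw no conclusion about PPV or NPV in screening use from them. Qualify the explanation in section 3.3.2 accordingly.

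No extra participants are needed; the cost is modest extra analysis. Setting-specific estimates will be less precise. At a rate of 0.60, 40 people give a standard error of sqrt(0.6 x 0.4/40) = 0.08; if a cell split evenly by setting, 20 would give 0.11. Recruitment by word of mouth supplies no sampling frame, so the target mixes must be assumed or taken from elsewhere. The reported figures may look less favourable.
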